# FACT: a randomised controlled trial to assess the feasibility of QbTest in the assessment process of attention deficit hyperactivity disorder (ADHD) for young people in prison—a feasibility trial protocol

**DOI:** 10.1136/bmjopen-2019-035519

**Published:** 2020-01-20

**Keywords:** child & adolescent psychiatry, forensic psychiatry, clinical trials, qualitative research

## Abstract

**Introduction:**

The prevalence of attention deficit hyperactivity disorder (ADHD) within the Children and Young People Secure Estate (CYPSE) is much higher than seen in the general population. To make a diagnosis of ADHD, clinicians draw on information from multiple sources, including parents and teachers. However, obtaining these is particularly difficult for young people in the secure estate. There is increasing evidence in the community that QbTest is able to assist in the accurate and earlier diagnosis of ADHD. The objective of this study is to assess the feasibility and acceptability of QbTest in the assessment of ADHD within the CYPSE.

**Methods and analysis:**

A single-centre parallel group feasibility randomised controlled trial will be conducted. Sixty young people within the CYPSE identified as displaying possible symptoms of ADHD will be randomised to the intervention arm (n=30; QbTest plus usual care) or control arm (n=30; usual care). Primary analyses will be descriptive and a process evaluation will be conducted to assess the contexts involved in implementing the intervention. Interviews will be conducted to explore acceptability and thematic analysis will be used to analyse the data.

**Ethics and dissemination:**

This study was approved by National Health Service Wales research ethics committee 3 (18/WA/0347) on 15 February 2019. The findings will be published in peer-reviewed journals, presented at relevant conferences and disseminated to the public via summaries cocreated with our patient and public involvement group.

**Trial registration number:**

ISRCTN17402196

Strengths and limitations of this studyThis trial is novel as it is one of the first trials within the Children and Young People Secure Estate.Understanding the effects of context as barriers or facilitators is critical for interpreting the findings.The study will engage meaningfully and substantively with a patient and public involvement group to ensure that the research and intervention are both feasible and acceptable.This is a feasibility trial and is not powered to show effectiveness of the intervention.This feasibility trial is only being conducted in one site.

## Introduction

In England, children and young people aged 10–17 years old remanded or sentenced into custody are placed in a variety of different secure establishments, known collectively as the Children and Young People Secure Estate (CYPSE). The CYPSE includes: Secure Children’s Homes, Secure Training Centres and Young Offenders Institutions (YOIs). The majority of young people are placed within the YOIs and there are four establishments in England accepting 15–17 years old.

The prevalence rate of attention deficit hyperactivity disorder (ADHD) in the CYPSE is approximately 30%–40%, which is significantly greater than the rate of 5%, seen in the general population.^1 2^ However, a report raised significant concerns about undetected neurodisability, including ADHD within the CYPSE, due to a lack of appropriate screening and assessment processes and training of staff.^3^ Additionally, many young people have comorbid mental health needs contributing to complexity in the assessment process. ADHD is associated with a range of poor outcomes, including a greater risk of developing other mental and physical health needs, educational and occupational problems and offending.^4–13^ The social and economic burden of untreated ADHD on society is significant.^14–19^

The publication of the Healthcare Standards for Children and Young People in Secure Settings^20^ attempted to provide a more standardised approach to the assessment and care provided within the CYPSE. One way was to recommend the use of the Comprehensive Health Assessment Tool (CHAT).^21^ The CHAT was introduced into the CYPSE in 2013 and is completed within all CYPSE sites in England, UK. The CHAT is a semistructured assessment of health needs, delivered by a nurse during the first 10 days of admission. If a nurse from talking with the young person and from observing them believes that they may have a need around difficulty concentrating, restlessness, fidgeting, and so on, then the nurse would recommend in the CHAT care plan that the young person be referred for a full ADHD assessment.

For a formal clinical diagnosis of ADHD, a key aspect is the use of information from informants such as parents, teachers and health professionals.^6 7^ However, access to such information can be difficult to obtain and take a long time to receive, resulting in delays to receiving a confirmed diagnosis. The number of days young people spend in the CYPSE is relatively short.^22^ Therefore, informant information is very often not received before the young person leaves and returns back to the community. There is also evidence from a recent review within the CYPSE that establishments find it difficult to provide interventions to young people who are sentenced to fewer than 6 months, due to delays in assessment and/or diagnosis.^23^ All these factors can lead to delays in young people with ADHD receiving a diagnosis and accessing evidence-based treatment.

The impact of missed opportunities in diagnosis and accessing appropriate treatment can be significant. Young people with untreated ADHD in the CYPSE have been found to have an eightfold increased frequency of aggressive incidents in secure settings.^24 25^ Reducing violence and aggression is a key priority for Her Majesty’s Prison & Probation Service and Ministry of Justice, given the increasing rates within prisons.^26^ Treatment of adult offenders with ADHD using medication has demonstrated a reduction in reoffending of up to 41%.^27^ Therefore, there are also likely social and economic benefits to improving the diagnosis and access to treatment for young people with ADHD in the CYPSE.

QbTest (Qbtech) is a computer task that measures three core aspects of ADHD: attention, impulsivity and motor activity. Performance on the task provides information (via an immediate report) on the three symptom domains of ADHD and a ‘summary score’ based on deviation from a normative data set based on age group and gender. QbTest can be used with individuals with mild learning disabilities as instructions on how to complete the task are visual. Practitioners use the information from the QbTest report in conjunction with the clinical information (patient history, observation and ADHD symptom questionnaire) to inform their decision whether the young person has ADHD or not.

QbTest demonstrates good psychometric properties^28 29^ and has the additional benefit over other computer tasks of measuring activity level, a core symptom of ADHD.^30^ There are several studies that demonstrate the clinical utility of QbTest in aiding diagnosis.^31 32^ A recent randomised controlled trial found clinicians with access to the QbTest report were more likely to reach a diagnostic decision about ADHD. At 6 months, 76% of those with a QbTest report had received a diagnostic decision, compared with 50% without a QbTest report. QbTest reduced appointment length, increased clinicians’ confidence in their diagnostic decisions and doubled the likelihood of excluding ADHD.^33^

The use of the QbTest in the community looks promising.^34^ However, there are a number of unknowns in relation to its use in the CYPSE. Implementing new approaches can require more planning due to the regime; therefore, the potential barriers and facilitators to implementation need to be understood. The young people within the CYPSE are more complex and have greater comorbidity than young people accessing community Child and Adolescent Mental Health Services. The acceptability of the QbTest needs to be assessed to see if the same positive findings can be replicated. Primary outcomes in previous QbTest trials^33^ have been time to diagnosis, but given the comparative short stay in the CYPSE and difficulty obtaining these data once they leave, it is unclear how reliably these data can be collected and/or if other outcomes, such as in aggressive incidents, are more important in this population.

The longer term aim is to undertake a definitive randomised controlled trial of the effectiveness of QbTest in the assessment of ADHD in the CYPSE. An evidence base within the CYPSE needs to be developed in order to change policy and implement the QbTest across the whole system. In line with the Medical Research Council (MRC) guidelines on developing complex interventions and as randomised controlled trials within the CYPSE are scarce, a feasibility study is required.^35^

### Trial objectives

To conduct a pragmatic feasibility randomised controlled trial to assess the feasibility and acceptability of QbTest in the assessment of ADHD within the CYPSE.

### Trial design

A parallel two-group randomised controlled trial with 1:1 individual participant allocation to QbTest plus usual care (n=30; intervention group) or usual care alone (n=30; control group) with a parallel process evaluation. Recruitment started in March 2019 and is due to last 12 months.

## Methods and analysis

### Setting

The study will be conducted in one YOI site within the CYPSE, in England.

### Eligibility criteria

#### Inclusion criteria

Identified as presenting with ADHD symptoms via the CHAT.Aged 15–18 years old.

#### Exclusion criteria

On remand (uncertain/sudden release).Non-English speaking (for pragmatic reasons, but will be included in the main trial testing applicability more widely).Previous or current confirmed diagnosis of ADHD.Currently receiving ADHD medication.Deemed to present risk to either the researcher or the staff.Unable to provide informed consent (over 16).Parental/legal guardian consent not received (under 16).

Potential participants will be identified by the prison healthcare team. The CHAT will identify potential participants displaying possible symptoms of ADHD, for example, any ADHD symptom codes in CHAT. Sentence status is accessible to healthcare staff via SystmOne (SystmOne is the clinical record system used within the CYPSE) and young people on remand will be excluded. Healthcare records will also be searched for previous or current confirmed diagnosis of ADHD and/or currently receiving ADHD medication and those young people will be excluded. The risk presented by potential participants will be assessed by the healthcare team, based on knowledge of the young person, information contained on SystmOne and discussion with prison staff and will take account of the likely risk in prison and community settings. Potential participants whose risk cannot be managed safely will be excluded.

### Usual care

The CHAT is a semistructured assessment of health needs. It is delivered by a nurse during the first 10 days of admission and includes assessing ADHD needs (not diagnostic) based on clinical history and observation of the young person. Young people identified with potential ADHD on the CHAT are discussed with the psychiatrist at the multidisciplinary team. ADHD questionnaires (self, teacher and parent) are completed and reviewed. If further ADHD assessment is required, this includes clinical assessment (history and observation) and obtaining informant information including developmental history (completed by nurse and psychiatrist). This typically involves a minimum of three appointments with the young person and liaison with teachers/parents.

### Intervention: QbTest plus usual care

Once the young person has been referred to the multidisciplinary team, the young person is booked into the QbTest clinic. The healthcare team will conduct the QbTest and use the information from the QbTest report in conjunction with the clinical information (patient history, observation and ADHD symptom questionnaire) to inform their decision whether the young person has ADHD or not. Young people randomised to the QbTest will receive usual care, as outlined above plus the QbTest. The QbTest takes approximately 20 min to complete and the results will be discussed with the psychiatrist and the young person; this will take approximately 10 min.

### Primary outcomes

Eligibility rate recorded as the number of eligible young people against the total number of young people identified with ADHD needs.Recruitment rate recorded as the number of eligible young people who consent to participate.Acceptability of randomisation recorded as the number of young people randomised.Acceptability of trial participation recorded as the number of eligible young people who drop out after receiving allocation.Attrition rate recorded as the number of young people who consent to participate that remain in the study until the end of follow-up at 6 months.

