### Sample size and recruitment

The required sample is 60 young people, 30 per study arm. This is large enough to test the feasibility of the research procedures and to establish a mean and SD on each outcome measure.^42^ Five young people are to be randomised into the study each month. Recruitment rates and the final target will be used to inform the decision to proceed to a definitive trial.

Attrition will be minimised by having robust trial procedures to prevent data loss. Procedures have been developed with our patient and public involvement (PPI) groups and tested for maintaining contact with participants. Recognising that this population can be difficult to follow-up, follow-up data collection points will occur within broad time windows. Having very broad time windows allows for as many follow-ups to be completed within the CYPSE, but also ensuring that no young people are excluded from the study if they miss a follow-up.

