### Data collection

QbTest completion rates: a record will be taken of the numbers of participants who agree to sit and also complete the QbTest.

QbTest opinion questionnaire: all young people who receive QbTest will be asked to complete the QbTest opinion questionnaire at 3 months. The questionnaire contains 11 questions, for example, ‘the QbTest results were difficult to understand’ and the young person is asked to rate each item on a 5-point scale. At month 15, clinicians involved in the QbTest will be asked to complete the clinician version, which contains 13 questions rated on a 5-point scale and two free-text response questions.^29^

Interviews with young people: randomisation: a subsample of young people in both trial arms will be interviewed using a semistructured interview schedule to further explore acceptability of the randomisation process. Young person’s age and time of randomisation (beginning or end of study) will be used to purposively select the sample. Outcomes: a subsample of young people in both trial arms will be interviewed using a semistructured interview schedule to further explore acceptability of completion of the outcome measures. Young person’s age and time of randomisation (beginning or end of study) will be used to purposively select the sample. QbTest: a subsample of young people who receive QbTest will be interviewed using a semistructured interview schedule to further explore acceptability of the QbTest and its administration as well as study processes and procedures. Scores/responses in the QbTest opinion questionnaire, young person’s age and whether or not the QbTest was completed will be used to purposively select the sample. Up to 20 young people will be interviewed.

Interviews with healthcare professionals and CYPSE staff: healthcare professionals and CYPSE staff will be invited to participate in qualitative interviews to further explore acceptability and feasibility of administering and implementing the QbTest within usual assessment practices and procedures, including the barriers to its use and reasons for non-completion. Scores/responses in the QbTest Opinion Questionnaire will be used to purposively select healthcare professionals. Up to 10 professionals will be interviewed.

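### Missing parental consent is counted as ineligibility rather than non-recruitment, and acceptability of randomisation is a bare count with no denominator

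*Protocol article*

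**What the plan says.** All references are to the protocol article.

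- **Primary outcomes.** The eligibility rate has a stated denominator: everyone identified with possible ADHD needs. The next item is "Recruitment rate recorded as the number of eligible young people who consent to participate". The third is "Acceptability of randomisation recorded as the number of young people randomised". Neither of these two has a written denominator. A further primary outcome counts those who drop out once they know their allocation.
- **Exclusion criteria.** The list includes "Parental/legal guardian consent not received (under 16"). For older participants it excludes inability to consent, which the Consent process section treats as a matter of capacity. Declining to take part is not listed.
- **Table 1.** The eligibility screen, informed consent and parental consent are separate enrolment lines, and all come before allocation.
- **Sample size and recruitment.** "The required sample is 60 young people, 30 per study arm", and "Five young people are to be randomised into the study each month". On their use: "Recruitment rates and the final target will be used to inform the decision to proceed to a definitive trial".
- **Data collection (process evaluation).** For views on being randomised, the plan is that "a subsample of young people in both trial arms will be interviewed using a semistructured interview schedule to further explore acceptability of the randomisation process".

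**The concern.** A feasibility trial should show where potential participants are lost, so that the definitive trial can deal with the right barrier. Two stated definitions work against this.

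First, Table 1 treats parental consent as a consent step, while the exclusion list treats its absence as ineligibility. If the list is followed, a willing 15-year-old whose parent refuses or cannot be reached is recorded as ineligible. The eligibility rate falls, the recruitment proportion rises, and the loss appears to come from the population instead of from the consent process. The Introduction already says that information from parents and other informants is hard and slow to obtain in this setting, so difficulty in reaching parents is a plausible barrier that the trial should be able to show.

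Second, the number randomised measures accrual. A trial that meets its target records about 60 whether most or few of those asked were willing to be randomised. The interviews on randomisation do not fill this gap, because everyone in a trial arm has already accepted it.

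**Working it through.** **The plan's own figure.** "Recruitment started in March 2019 and is due to last 12 months". Five a month for 12 months is 5 × 12 = 60, and 30 + 30 = 60. The target reproduces. There is no power calculation to check.

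**Parental consent.** The age range is 15 to 18, so the under-16 rule reaches 15-year-olds only. The article gives neither their share nor the parental consent rate, so the following inputs are assumptions: 100 identified, 80 eligible apart from parental consent, 48 consenting, and half of under-16s lacking parental consent.

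Let s be the share of the 80 aged under 16 and m the proportion of those without parental consent.

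- Eligible as the plan counts: 80 × (1 − s × m)
- Eligibility rate as the plan counts: that number / 100
- Recruitment as the plan counts: 48 / that number
- Counting missing parental consent as non-recruitment: eligibility 80/100 = 80%, recruitment 48/80 = 60%

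| s | m | Eligible as planned | Eligibility rate | Recruitment |
|---|---|---|---|---|
| 5% | 50% | 80 − 2 = 78 | 78% | 48/78 = 61.5% |
| 20% | 50% | 80 − 8 = 72 | 72% | 48/72 = 66.7% |
| 10% | 30% | 80 − 2.4 = 77.6 | 77.6% | 48/77.6 = 61.9% |
| 30% | 70% | 80 − 16.8 = 63.2 | 63.2% | 48/63.2 = 75.9% |

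Overall yield from those identified is the same under either count: 0.72 × 0.667 = 0.48 and 0.80 × 0.60 = 0.48.

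A second set of assumptions gives a similar picture. Take 150 otherwise eligible, with half of the young people themselves willing, and parental consent obtained for 20% to 80% of under-16s. The plan's recruitment proportion stays at 50% whatever parents do. Counting missing parental consent as non-recruitment gives 48% to 49.5% if 5% are under 16, and 38% to 47% if 30% are. The inflation is therefore 0.5 to 12 percentage points.

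**Acceptability of randomisation.** The number approached is not given, so these denominators are assumptions. The intervals are exact (Clopper-Pearson) 95% intervals.

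| Approached | Recorded by the plan | Proportion accepting (95% CI) |
|---|---|---|
| 75 | 60 | 80% (69 to 88) |
| 100 | 60 | 60% (50 to 70) |
| 150 | 60 | 40% (32 to 48) |
| 300 | 60 | 20% (16 to 25) |

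The item as worded gives the same result in all four rows.

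**The case against.** The strongest reply is that the primary outcomes are meant to be read together. The eligibility rate supplies the number eligible, so randomised/eligible can be worked out even though it is not written. This largely stands. It does not fully rescue the item, because the number eligible already omits 15-year-olds without parental consent, and the article does not say that every eligible person is approached.

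A reader might also infer three stronger claims, which the article does not support.

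- *That refusals in general are defined out.* They are not. A young person who declines remains eligible and is not counted as consenting, so own refusals equal eligible minus consenting. Only missing parental consent is moved.
- *That the count is capped at 60.* Sixty is called the required sample and the target, and no ceiling is stated. A shortfall would still show that accrual was missed, though not whether randomisation was the reason.
- *That nothing else bears on acceptance of randomisation.* Drop-out after allocation is a separate primary outcome and is relevant. Like the interviews, though, it concerns only people who had agreed to be randomised.

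It is also fair to say that the parental-consent rule moves a loss between two reported rates without hiding it, and that a parent's refusal says nothing about the young person's willingness. Finally, the sentence on the decision to proceed names recruitment rates and the target, not acceptability of randomisation, although the Discussion does rest the decision on adequate feasibility and acceptability.

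**Conclusion.** The point holds in a narrow form and is a cheap improvement. Under the stated rules, a consent failure among 15-year-olds is recorded as ineligibility. Total yield is unaffected, but the barrier is misattributed and the recruitment proportion is raised. In the first illustration the rise is 1.5 points if 5% are under 16 and 6.7 points if 20% are, with half lacking parental consent. It is small if few are aged 15. Every size given here rests on assumed shares and consent rates.

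The second part needs no assumption: a count of those randomised, as the primary outcome is defined, measures accrual and not acceptability. The associated interviews cannot correct this, because they exclude anyone who declined.

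**What to change.** 1. Keep parental or guardian consent as a condition of entry for under-16s, but take its absence out of the eligibility count and record it as eligible, not recruited. Only the counting changes.
2. State the recruitment rate as consented/eligible, with a 95% confidence interval.
3. State acceptability of randomisation as randomised/eligible approached, with a 95% confidence interval, and give the number who declined because of randomisation where a reason is volunteered.
4. Do not use randomised/consented as the main measure. Consent precedes allocation, so most objections to randomisation would surface at consent and this ratio should be near 100%.

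The cost is the rewording of two outcome definitions and one criterion, and one optional field on the screening log. The reported recruitment rate may look slightly less favourable. Recruitment has already begun, but where screening counts by reason have been kept, the ratios can still be reported.
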